	Complications								x	Clavien-Dindo minor: I-II major: III-V
	Reoperations								x	EHR
	Readmission ≤30 days								x	EHR
	In-hospital mortality								x	EHR
Gastrointestinal	Tolerance of solid food				O					Days
	Absence of nausea				O					Days
	Passage of first flatus				O					Days
	Passage of first stool				O					Days
	Weight - preoperative			x						Weight at admission, KG
	Weight - at discharge				x					Weight at discharge, KG
Activity	Mean preoperative physical activity (steps/day)		O							Activity tracker, steps per day
	Postoperative physical activity (steps/day)				O	O	O			Steps per day
Pain	Perceived pain daily postoperative - discharge				O					NRS 1–10*
	Compliance with intake of (pain) medication				O					Y/N questions in app or with paper form
Self-registered questionnaires		T0	T1	T2	T3	T4	T5	T6	T7	
PROMS	General quality of life (WHOQol)	x				x	x		x	WHOQoL - BREF
	Multidimensional fatigue assessment	x						x	x	Multidimensional fatigue inventory
	Physical Activity (IPAQ)	x				x		x	x	IPAQ-short
	Disability	x							x	WHODAS2
	Patient satisfaction questionnaire								x	Self-developed patient satisfaction questionnaire

T0: Moment of randomization; T1: 1–7 days before stay in hospital; T2 hospital admission; T3: day of surgery; T4: 1–7 days after surgery; T5: 8–14 days after surgery; T6: 15 days – 21 days after surgery; T7: 22–42 days after surgery

x: the event/action is performed or assessed once in the indicated time slot. O: the event/action is performed or assessed continuously in the indicated time slot. *Numeric rating scale

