### Data analyses

Statistical analyses of any difference between the two study groups will be performed using SPSS for Windows version 25 or higher (SPSS Inc. Chicago, IL). Data will be analysed according to intention to treat protocol. If applicable, missing data will be imputed. Baseline characteristics will be summarized using descriptive statistics and compared between the intervention and control groups. Continuous data will be reported as mean and standard deviation in case of normal distribution and as median 95% confidence intervals in case of non-normal distribution. Normality of the data distribution will be analysed by visually inspecting the histograms and Kolmogorov-Smirnov test. Comparative analysis will be done using a two-sided t-test in case of normal distribution and by means of the Mann-Whitney U test in case of non-normal distribution. *P*-values of ≤0.05 will be considered statistically significant.

Categorical data will be displayed as numbers and percentages and analysed using a Chi-square test.

Investigational site, surgical procedure, age, and score on the eHealth literacy test will be taken into account as covariates in the adjusted analyses. Intended subgroup analyses will be conducted for the surgical procedure.

To estimate the primary outcome, the overall average compliance to the selected active ERAS elements, the elements will be scored as ‘completed’ or ‘not completed’ (dichotomous), as described by the ERAS protocol. For example, the urine catheter should be removed on day one after surgery. If this could not take place, the element was scored as ‘not completed’. For both the intervention and control groups, the proportion of completion of each individual active element will be calculated. The overall compliance is an average of the individual completion percentages. The protocol compliance is a continuous variable and will be reported as mean and standard deviation in case of normal distribution and as median and 95% confidence intervals in case of non-normal distribution.

The relation of the use of the application with the secondary outcomes mentioned in Table 5 will be examined with a linear regression.

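### The protocol names linear regression for every Table 5 secondary outcome, does not reconcile it with its other tests, and leaves the T0 value of four patient-reported outcomes out of the stated covariates

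*Protocol article*

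**What the plan says.** All the rules stand in the Data analyses section of the protocol article.

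- Continuous data: "Comparative analysis will be done using a two-sided t-test in case of normal distribution and by means of the Mann-Whitney U test" if the distribution is not normal.
- Categorical data: "Categorical data will be displayed as numbers and percentages and analysed using a Chi-square test".
- Adjustment: "Investigational site, surgical procedure, age, and score on the eHealth literacy test will be taken into account as covariates in the adjusted analyses".
- Secondary outcomes as a block: "The relation of the use of the application with the secondary outcomes mentioned in Table 5 will be examined with a linear regression".

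The section also states analysis by intention to treat.

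Table 5 (Outcomes section) defines the secondary outcomes:

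- **Binary events:** for example "Readmission ≤30 days", reoperations and in-hospital mortality.
- **Complications:** Clavien-Dindo grades grouped as "minor: I-II major: III-V".
- **Recovery events counted in days:** for example "Passage of first flatus", first stool, tolerance of solid food and absence of nausea. Length of hospital stay is listed too.
- **Patient-reported outcomes with a T0 value:** WHOQoL-BREF (T0, T4, T5, T7), the fatigue inventory (T0, T6, T7), IPAQ (T0, T4, T6, T7) and WHODAS2 (T0, T7). The footnote defines T0 as the moment of randomisation.
- **Patient satisfaction:** T7 only.

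**The concern.** Three things are fixed poorly.

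First, one model type is named for outcomes of different kinds. A linear model with covariates does not keep fitted risks between 0 and 1. It also has no rule for a patient who dies, withdraws or is last seen before first stool or solid food.

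Second, the regression stands beside the other tests with no order of precedence. Readmission, for instance, falls under both the chi-square rule and the linear regression. If the two disagree around the 0.05 threshold, the protocol does not say which is the result.

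Third, the covariate list leaves out what is usually the strongest predictor of a questionnaire score, the same patient's score at randomisation. The Outcomes section calls quality of life an important secondary outcome, so precision there matters.

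The exposure also needs one clarifying phrase. Use of the application could be read as actual use, which is behaviour after randomisation.

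**Working it through.** **1. The plan's own figure.** Inputs from the Sample size calculation section: difference 62 − 57 = 5 points, SD 9, two-sided alpha 0.05, power 90%.

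n per group = 2(1.960 + 1.282)² × 9² / 5² = 68.1, so 69. The t-based calculation gives 69.06, so 70. Allowing for 10% loss, 140 / 0.9 = 155.6, so 156. The stated figures reproduce. They concern the primary outcome only; the article gives no precision figure for secondary outcomes. Below, 70 evaluable patients per arm is carried over to them as an assumption.

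**2. Value of the T0 score.** With correlation ρ between T0 and follow-up (assumed), ANCOVA multiplies residual variance by 1 − ρ² and confidence interval width by √(1 − ρ²), compared with no adjustment. The detectable difference at 80% power without T0 is (1.960 + 0.842) × √(2/70) = 0.474 SD; with T0 it is multiplied by √(1 − ρ²).

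| ρ (assumed) | Variance cut | CI width cut | Detectable difference | Power at an illustrative 0.4 SD |
|---|---|---|---|---|
| no T0 | – | – | 0.474 SD | 66% |
| 0.3 | 9% | 5% | 0.452 SD | 70% |
| 0.5 | 25% | 13% | 0.410 SD | 78% |
| 0.7 | 49% | 29% | 0.338 SD | 91% |

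The comparison is with an unadjusted analysis. Age, procedure, site and eHealth literacy may already explain part of the same variance, so the added gain over the listed covariates may be smaller.

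**3. Linear regression on a binary outcome.** Simulation with 70 per arm and 3,000 trials per setting. Covariates were of the listed kinds, and age was given an effect on risk. Event rates are assumed.

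| Event rate, control / app | Rejections, linear | Rejections, chi-square | Trials with a fitted risk outside 0 to 1 |
|---|---|---|---|
| 2% / 2% | 2.7% | 2.8% | 96% |
| 10% / 10% | 4.9% | 4.9% | 93% |
| 30% / 30% | 4.9% | 5.1% | 61% |
| 30% / 15% | 54.8% | 55.0% | 87% |

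The first three rows show type I error and the last shows power. The two methods agree closely on both. What fails is the fitted risk: in 61% to 96% of trials at least one patient's value was impossible. Interval coverage was not examined.

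**4. Skewed length of stay.** Simulation with a log-normal stay, 20% shorter in one arm, and log-SD 0.5, 0.7 or 0.9 (all assumed). The t-test, which equals unadjusted linear regression on arm, had power of 69%, 39% and 24%. Mann-Whitney had 72%, 44% and 30%. With no difference, the t-test rejected in 5.4%, 5.0% and 3.8%. The linear model loses some power and does not inflate false positives. Death and incomplete follow-up were not simulated.

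**The case against.** The strongest reply is that the regression is not the only analysis. The section opens with comparisons between the two groups and already gives chi-square for categorical data and Mann-Whitney for non-normal data. The regression may be meant as an additional, adjusted look. This stands in part: a reader might infer that every secondary outcome is tested by linear regression alone, and the text does not support that. The defect is two methods left unreconciled, one of which does not suit part of the list.

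A reader might also infer more than the article supports on five further matters:

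- **False positives for binary events.** The check above shows rejection rates close to chi-square, so inflated error cannot be claimed.
- **Satisfaction.** It has no T0 value, so nothing is lost by leaving one out.
- **Breach of intention to treat.** Controls have no application, the Abstract uses similar wording for the intervention itself, and intention to treat is stated. Allocated arm is the natural reading, and only a clarification is needed.
- **Unfinished recovery times.** That some patients will not reach the event under observation is plausible, but the article neither states nor quantifies it.
- **T0 expressly excluded.** It is absent from the stated list, not ruled out, and a fuller plan may add it. An analysis without it is still valid in a randomised trial; the loss is one of precision.

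**Conclusion.** The point holds as a recommended correction, not as an error that invalidates the trial. The protocol fixes one model type for a mixed list of outcomes, does not order it against its other tests, and names covariates without the randomisation score of four questionnaires.

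The main measurable loss is precision on those four. Its size rests on an assumed correlation of 0.3 to 0.7, on 70 evaluable patients per arm, and on a comparison with no adjustment. It could be modest at the lower end. For binary outcomes the benefit of a suitable model lies in the effect scale and in possible fitted risks, with little change in type I error or power. For days to recovery the benefit depends on how many patients do not reach the event, which the article does not give.

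**What to change.** Replace the single regression sentence with rules by outcome type:

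- **Exposure:** the allocated arm, in line with intention to treat.
- **WHOQoL-BREF, fatigue inventory, IPAQ:** a mixed model over the follow-up time points, or ANCOVA at a named one, with the T0 value as covariate. **WHODAS2:** ANCOVA at T7 with the T0 value.
- **Satisfaction:** a group comparison at T7 without baseline.
- **Readmission, reoperation, in-hospital mortality:** logistic regression or a risk-difference model, with an exact method where events are few.
- **Complications:** a binary model at a stated cut, or an ordinal model if none, minor and major are kept apart.
- **Days to recovery events:** a time-to-event method where the event may not be reached, with a stated rule for death and withdrawal.
- **Length of stay:** a method suited to skewed data, with a stated rule for death.
- **Linear regression:** continuous outcomes only.
- **Precedence:** for each outcome, say whether the simple test or the model is the main result.

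The cost is wording only. All the variables are already scheduled in Table 5, the target of 156 does not change, and the article reports that data collection had not begun at submission.

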### Prognostic factors

Preoperative baseline characteristics will be collected (sex, age, ASA classification, Body Mass Index (BMI), smoking, alcohol intake, Karnofsky scores, co-morbidity, indication for surgery and eHealth literacy will be assessed standardized).

### Potential confounders

Major per- and postoperative events, such as complications during surgery or a prolonged hospital stay due to complications in the postoperative course, readmission, or re-intervention within the 30 days follow up period after surgery, are considered as potential confounders. Direct caregivers, such as the nurse, are instructed to register potential confounders in the EHR. The coordination researcher will screen each participant for the EHR for per- and post-operative complications after the follow up period is completed.

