### Control and intervention group

#### APPtimize study group

Patients in the intervention group will receive instructions how to download the APPtimize application shortly after the operation is scheduled. The application will be used until 42 days postoperative. The selected ERAS elements (Table 2) have been translated into practical patient-tailored features that can be viewed in the application any time but will also be brought to the patient’s attention through push notifications (Table 3) at set times. The push notifications attempt to prompt the patient to undertake action towards an ERAS element that requires action at that specific moment. The main goals of the application are: to inform and educate the patient, to stimulate patient participation throughout the perioperative care pathway, and to monitor daily activity. All information provided by the application can be accessed at any moment but also once an ERAS element of the care pathway is considered completed. Figure 1 illustrates the layout of the application, with the third screenshot showing the application’s feature ‘dashboard’. This feature represents the completion of three subjects: 1. completion of the daily set activity goal 2. completion of the active ERAS elements, and 3. completion of self-registered questionnaires throughout the entire study.

**Table 3 Tab3:** Push notifications

Preoperative day	Notification
−21	Information about nutrition
−20	Information about smoking
−16	Information about preparation before surgery
−8	Instructions to wear the activity tracker
−2	No alcohol 24 h before surgery
−1	Instructions to drink the pre-operative nutrition drink (4x)
0	Instructions to drink the pre-operative nutrition drink (1x)
Postoperative day	Notification
0	Instructions to wear the activity tracker
1,2,3,..,day of discharge	information of daily goals
1,2,3,..,day of discharge	Information on progress of daily activity
1,2,3,..,day of discharge	Check progress to discharge in the overview of ‘completion of goals’

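### Retrospective record review is the only described source for 30-day complications, re-interventions and readmissions, so events treated elsewhere after discharge may be under-counted

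*Protocol article*

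**What the plan says.** The Outcomes section of the protocol article presents Table 5 as its account of what is measured, how and when. The table marks the 30-day postoperative block as collected retrospectively. It names the EHR as the source for overall morbidity, reoperations and readmission ("Readmission ≤30 days"), and for length of stay and in-hospital mortality. For complications it gives the grading, "Clavien-Dindo minor: I-II major: III-V", so minor events count as an outcome too.

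The method of finding events is under Potential confounders: "The coordination researcher will screen each participant for the EHR for per- and post-operative complications after the follow up period is completed". A supporting instruction precedes it: "Direct caregivers, such as the nurse, are instructed to register potential confounders in the EHR". Those confounders are defined as "Major per- and postoperative events, such as complications during surgery or a prolonged hospital stay due to complications in the postoperative course, readmission, or re-intervention", counted over a 30-day window from the operation.

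Patients in both arms complete self-registered questionnaires in the last time slot, "T7: 22–42 days after surgery". The article lists no item on complications, re-intervention or readmission among them.

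**The concern.** The trial runs at two locations of one university medical centre, and patients expected to stay 3 days or less are excluded. For a patient discharged in the first week or so, most of the 30-day window is spent at home. An event managed by a general practitioner or at another hospital need not reach the study centre's record, and a retrospective search finds only what was written there. Minor (grade I-II) complications after discharge are the most exposed.

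Two things are at stake. The absolute 30-day rates could be too low in both arms. The comparison could also be distorted: the window is fixed from surgery, so an arm with a shorter stay has more of it outside the hospital. Preparing for early discharge is one of the ten elements in the app (Table 2). If the app did shorten stay, the distortion would favour it.

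**Working it through.** **Plan's own figure.** No stated figure is in dispute, but the planned size sets the scale. A difference of 5, SD 9, two-sided alpha 0.05 and 90% power give 69 per arm by the normal approximation and 69.06, rounded up to 70, by the t-test. Then 140/0.9 = 155.6, so 156. The sample size reproduces and this point leaves it unchanged.

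**What the passages cover.**
- Source of outcome data: the EHR, searched by the coordinating researcher after follow-up. The search is for complications in general and is not limited to major ones.
- Caregiver instruction: major events, with readmission and re-intervention within 30 days named.
- Care given elsewhere: the article does not say whether the EHR shows it or whether outside records are requested.
- Length of stay: the Conclusion says only that it and complication rates might improve. Neither arm is stated to leave earlier.

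**Size, under assumptions.** The documents give no complication rate, share of events after discharge or capture rate, so all three are assumed. Let p be the true 30-day rate (equal in both arms), s the share of events after discharge, and m the share of those missed.

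- Recorded rate = p × (1 − s × m)
- False difference (control minus app) = p × m × (s_app − s_control)

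*Under-count in both arms.*
- With s = 25% and m = 10% to 40%, the relative loss s × m is 2.5% to 10%.
- With p = 30%, s = one third and m = 40%, the loss is 0.30 × (1/3) × 0.40 = 0.04, or 4 of 30 points.

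*Difference between arms.*
- Equal shares after discharge: 0, whatever p and m are.
- Milder set (p = 20% to 40%, s_control = 25%, s_app = 30% to 35%, m = 10% to 40%): from 0.20 × 0.10 × 0.05 = 0.1 points to 0.40 × 0.40 × 0.10 = 1.6 points.
- Wider set (p = 30%, shift of 5 to 20 points, m = 10% to 50%): from 0.30 × 0.05 × 0.10 = 0.15 points to 0.30 × 0.20 × 0.50 = 3.0 points.

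*Random error for comparison.* The standard error of a difference in proportions is √(2p(1 − p)/70). It is 6.8 points at p = 20%, 7.7 at 30% and 8.3 at 40%. The largest false difference, 3.0 points at p = 30%, is 3.0/7.7 = 0.39 of a standard error.

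**The case against.** The best defence is that a journal article condenses a longer protocol, which may provide for letters from general practitioners, outside records or case report form items. The EHR may itself hold such correspondence, and the content of the self-developed satisfaction questionnaire at T7 is not shown. This stands as a reason to speak of events that may be missed. It does not dispose of the point, because the article presents Table 5 as describing how every outcome is measured, and both it and the Potential confounders section point to the EHR alone. That is a stated method, not an omitted detail.

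A reader might make four stronger inferences, which the document does not support:
- *That events are missed.* The text establishes a risk. It does not say what the EHR contains.
- *That the word major limits which complications are counted.* It defines the confounders that caregivers register. The researcher's search, which supplies the outcome, has no such limit, and the instruction already covers readmission and re-intervention to day 30.
- *That the app arm will look safer than it is.* This needs an actual difference in length of stay, which the article does not predict.
- *That the record review must run to day 42 because "The application will be used until 42 days postoperative".* The period of app use is not the outcome window, which is 30 days.

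The remedy also carries a risk. Self-report would come through the app in one arm and on paper in the other, in an unblinded trial, so completion could differ by arm. That stands and is addressed in the fix.

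**Conclusion.** The point holds in limited form. The only described source for 30-day complications, re-interventions and readmissions is a retrospective EHR review, so events treated outside the two locations after discharge may be under-counted in both arms. This needs no difference in length of stay, only that some outside care does not reach the record.

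A difference in under-counting between arms is conditional on a difference in stay. Under the assumed ranges it is about 0 to 3 percentage points, less than half a standard error. It would be systematic, so it does not average out, but it is unlikely to decide a comparison in a trial of this size. Only secondary outcomes are touched. Length of the index stay is unaffected, as are the primary compliance outcome and the sample size. The case for acting is that the improvement is cheap and that an event which never reached the record cannot be recovered from it later.

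**What to change.** Add two or three items to the existing T7 questionnaire in both arms, worded identically in the app and on paper. They should ask about any readmission, re-intervention, or hospital or general-practitioner treatment for a complication since discharge, with date and place. Ask them no earlier than day 30: the T7 slot opens at day 22, and an earlier answer would not cover the window. Verify positive answers against records before grading, and report item completion by arm. Also state whether the EHR shows care given elsewhere.

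Optionally, word the caregiver instruction to cover all Clavien-Dindo grades, since grades I-II are also an outcome.

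The cost is a few questionnaire items and a few record requests. The downsides are recall error and possible differences in completion between app and paper. Data collection had not begun when the article was submitted, so at that stage the items could have applied to every participant.

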### Trial discontinuation and withdrawal

When a trial participant experiences unmanageable negative feelings caused by the use of the APPtimize application, such as anxiety or physical discomfort, discontinuation of participation to the APPtimize trial will be recommended. Patients are informed of their right to withdraw from the trial without explanation at any time. Withdrawn participants will be asked if data about their hospital admission can be collected and they will be asked to sign an informed consent if they agree to this data collection. Data collection of withdrawn participants consists of: general patient characteristics, eHealth literacy assessment, disease related characteristics and postoperative data.

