### Outcomes

The primary outcome is the overall average compliance to the selected active ERAS elements (Table 2). Since the application is patient-centred and focusses on empowering patients to get in control of their own health, the PROMs, such as health related quality of life and patient satisfaction, are considered important secondary outcome parameters. Other secondary outcomes include postoperative outcome parameters (e.g. complications), gastro-intestinal recovery (e.g. time to passage of stool), activity and pain measurements. Table 5 describes all study outcomes and how and when these will be measured.

**Table 5 Tab5:** Time points and measurements

Enrolment		T0	T1	T2	T3	T4	T5	T6	T7	Registered in/with:
	Eligibility screen	x								
	Informed consent	x								
	Allocation	x								
Interventions		T0	T1	T2	T3	T4	T5	T6	T7	
Intervention group	Download mobile application	x								
	Wear activity tracker		O	O	O	O	O	O		
Control group	Wear activity tracker		O	O	O	O	O	O		
Data measurements		T0	T1	T2	T3	T4	T5	T6	T7	
Baseline characteristics	General characteristics	x								Sex, age, ASA, BMI, smoking, alcohol intake
	Disease related characteristics	x								Disease, operation
	eHealth literacy assessment	x								eHEALS
Protocol compliance *(as reported by patients)*	1. Cessation of smoking and excessive intake of alcohol	x								Y/N questions in app or with paper form
	2. Preoperative nutritional screening and, as needed, assessment and nutritional support	x								Y/N questions in app or with paper form
	3. Preoperative carbohydrate treatment			x						Y/N questions in app or with paper form
	4. Preoperative prophylaxis against thrombosis			x						Y/N questions in app or with paper form
	5. Early mobilization (day of surgery)				O	O				Y/N questions in app or with paper form
	6. Early intake of oral fluids and solids (offered the day of surgery)				O	O				Y/N questions in app or with paper form
	7. Early removal of urinary catheters and intravenous fluids (morning after surgery)					O				Y/N questions in app or with paper form
	8. Use of laxatives					O				Y/N questions in app or with paper form
	9. Intake of protein and energy-rich nutritional supplements					O				Y/N questions in app or with paper form
	10. Prepare for early discharge					O				Y/N questions in app or with paper form
Postoperative data ≤30 days *(retrospective collection)*	Length of hospital stay								x	EHR
	Overall morbidity ≤30 days								x	EHR

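### Patients distressed by the app are advised to leave the trial, and compliance and PROMs are then not collected, so app-arm outcomes can be missing because of the app itself

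*Protocol article*

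**What the plan says.** All references are to the protocol article.

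- **Trial discontinuation and withdrawal.** If use of the app causes negative feelings that the patient cannot manage, "discontinuation of participation to the APPtimize trial will be recommended". Separately, and for both arms, "Patients are informed of their right to withdraw from the trial without explanation at any time".
- **Same section, data after withdrawal.** "Withdrawn participants will be asked if data about their hospital admission can be collected", with a signed consent if they agree. The content is then fixed: "Data collection of withdrawn participants consists of: general patient characteristics, eHealth literacy assessment, disease related characteristics and postoperative data".
- **Outcomes, Table 5.** Compliance with the ten elements is a block of its own, marked as patient-reported and answered in the app or on paper. Postoperative data up to 30 days (length of stay, morbidity, complications, reoperation, readmission, mortality) form a different block, collected retrospectively, mainly from the EHR. The PROMs form a third.
- **Data analyses.** "Data will be analysed according to intention to treat protocol". The next sentence provides for imputation of missing data where applicable.

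**The concern.** The app-specific trigger leads out of the trial, not merely out of the app. Control patients do not have the app, so this route exists in one arm only. Once a patient has left, the listed data cover neither the primary outcome nor the PROMs. Reading the listed postoperative data as including compliance does not fit Table 5, which keeps the two in separate blocks, and patient-reported answers cannot be recovered later from the record.

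Outcomes can therefore be missing because of a reaction to the randomised intervention. Intention-to-treat follow-up is meant to prevent exactly this kind of loss. If those who leave would have complied less or been less satisfied, the app arm is judged on patients who tolerated the app, and its results look better than they are. Imputation that treats leavers as similar to observed app users would carry the same bias.

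Satisfaction is the most exposed outcome. It is measured only at T7 (days 22–42), so anyone who leaves earlier contributes nothing to it.

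**Working it through.** **1. The plan's own figure.** From Sample size calculation: 57% against 62% (difference 5 points), SD 9, two-sided alpha 0.05, power 90%.

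- Normal approximation: n = 2 × (1.960 + 1.2816)² × 9² / 5² = 2 × 10.508 × 3.24 = 68.1, so 69 per group.
- t-test solution: 69.06, so 70 per group, as stated.
- With 10% loss: 140 / 0.9 = 155.6, so 156 in total, or 78 per arm, as stated.

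The sample size reproduces. The 10% loss is not split by arm or by reason.

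**2. What a leaver loses (Table 5).**

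| Item | When recorded | Lost if the patient leaves before then |
|---|---|---|
| Elements 1–2 | T0 | No, if data recorded before withdrawal are kept |
| Elements 3–4 | T2 (admission) | Yes, if leaving before admission |
| Elements 5–10 | T3–T4 (surgery to day 7) | Yes, six of ten elements |
| Satisfaction | T7 only | Yes, entirely |
| Final quality of life, fatigue, physical activity, disability | T7 | Yes |

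Patients in the app arm receive the app shortly after surgery is scheduled, and notifications begin at day −21 (Table 3), so leaving before surgery is possible. Leaving after day 7 costs no compliance data but still costs the T7 measures.

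**3. Size of the bias in a complete-case analysis.** Let w be the share of the app arm that leaves because of the app, g the number of points by which leavers fall below stayers, and S the mean of stayers.

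- Mean of the whole arm: (1 − w)S + w(S − g) = S − wg.
- Complete-case mean: S.
- Overstatement: w × g.

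The documents give neither w nor g. Assumed ranges: w = 2%, 5%, 10%; g = 5 (the target difference), 9 (one planning SD) and 18 (two SDs). For scale, one element out of ten is 10 points.

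The type I error assumes no true difference between the full arms, a fully observed control arm, SD 9 and SE = 9 × √(1/78 + 1/(78(1 − w))).

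| w (patients of 78) | g | Bias w × g (points) | Share of 5 points | Two-sided type I error |
|---|---|---|---|---|
| 2% (1.6) | 5 | 0.10 | 2% | 0.051 |
| 2% | 9 | 0.18 | 4% | 0.052 |
| 2% | 18 | 0.36 | 7% | 0.057 |
| 5% (3.9) | 5 | 0.25 | 5% | 0.053 |
| 5% | 9 | 0.45 | 9% | 0.061 |
| 5% | 18 | 0.90 | 18% | 0.095 |
| 10% (7.8) | 5 | 0.50 | 10% | 0.063 |
| 10% | 9 | 0.90 | 18% | 0.093 |
| 10% | 18 | 1.80 | 36% | 0.229 |

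With g = 0 the bias is zero and the type I error stays at 0.05.

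**4. Why g stops at 18.** A subgroup of share w lying g points lower adds variance w(1 − w)g². With w = 10%:

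- g = 18: 0.09 × 324 = 29.2, or 36% of 9² = 81.
- g = 20: 0.09 × 400 = 36, or 44%.
- g = 30: 0.09 × 900 = 81, the whole planning variance, leaving none for differences among the other patients.

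Gaps of 20 to 30 points therefore fit poorly with the protocol's own SD.

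**The case against.** Several stronger statements are tempting, and the protocol does not support them.

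- **That intention to treat is impossible under this rule.** A reader might infer this, but the protocol provides for imputation, so withdrawn patients can stay in the analysis in their randomised arm. The imputation method is commonly left to the SAP, which is not shown, and its absence is no finding. What stands is that any imputation would have to make up for outcomes lost through a reaction to the app, and observed app users are a doubtful basis for that.
- **That the app arm is known to shed its failures.** No text says that distressed patients comply less, or how many there would be. Control patients may also withdraw, and they carry a tracker and a daily diary, so their losses may be selective too. The mechanism is specific to one arm; the net direction is not proven.
- **That anyone who stops the app is out of the trial.** The rule covers one narrow case, and leaving is advised, not imposed. Nothing removes a patient who merely stops using the app.
- **That all ten elements are lost.** Elements 1–4 may already be recorded, and the article does not say that such data are discarded.

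These points limit the size and certainty of the concern. They do not remove it: for the case the rule does cover, the protocol advises exit from the trial and then does not list the primary outcome among the data collected.

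**Conclusion.** The concern holds in a limited form. Following the withdrawal rule can make primary outcomes and PROMs missing in the app arm for a reason tied to the randomised intervention. The intention-to-treat comparison would then rest on imputation under a doubtful assumption and may favour the app.

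Under the assumptions shown, the overstatement ranges from negligible (0.1 points) to about a third of the target effect (1.8 points). The upper end needs the whole planned 10% loss rate in the app arm to be due to app distress, together with a gap of two SDs. No figure can be given for satisfaction or quality of life, but satisfaction is wholly unobserved for anyone who leaves before T7.

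The loss is avoidable, because compliance can already be recorded on paper without the app.

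**What to change.** Leave untouched when a patient should stop using the app; that is a clinical matter. Change only what happens to follow-up.

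1. In Trial discontinuation and withdrawal, distinguish stopping the app from withdrawing from the trial. Patients who stop the app are asked to remain in follow-up, using the paper checklist and questionnaires that the control arm already completes, and are analysed in their randomised arm.
2. For patients in either arm who withdraw fully, keep compliance recorded before withdrawal where consent allows.
3. Add a sensitivity analysis that scores the missing elements of withdrawn patients as not completed. This is a harsh bound, not an estimate: a leaver with nothing recorded counts as 0, so at the planned app-arm mean of 62 each 1% of the arm lowers its mean by 0.01 × 62 = 0.62 points.

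Compliance should not be filled in from the EHR. Table 5 defines it as patient-reported and assigns none of the ten elements to the EHR, so doing this for some app-arm patients would change the source of the outcome in one arm.

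The cost is small: wording in the withdrawal section, the patient information form and the CRF, and a switch from app to paper recording for a few app-arm patients. The sample size does not change. The change belongs before enrolment, since patient-reported answers not collected at the time cannot be recovered.
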